## **7 STUDY PROCEDURES AND ASSESSMENTS**

Refer to Appendix 2 – Schedule of Procedures, for a summary of required study activities.

### **7.1 Informed Consent/Assent**

Prior to conducting any tests or procedures performed solely for the purposes of the study, written informed consent, and assent if applicable, must be obtained from the subject and/or subject's legal representative.

### **7.2 Demography**

Demographic information (including date of birth, sex, race and ethnicity) will be transferred from the Immunotherapy Registration Portal at Screening.

### **7.3 Medical History**

Relevant medical history, including history and treatment of CNS disease, will be obtained per the Schedule of Procedures.

### **7.4 Performance Status**

Lansky (for subjects < 16 years of age) or Karnofsky (for subjects  $\geq$  16 years of age) performance status will be assessed per the Schedule of Procedures. Subjects who are unable to walk because of paralysis, but who are up in a wheelchair, will be considered ambulatory for purposes of assessing performance status. Reference Appendix 3 – Performance Status Scales.

### **7.5 Physical Examination, Vital Signs, Weight, Height**

Physical examinations, vital signs (must include pulse, respiratory rate, blood pressure and temperature), weight and height will be done per the Schedule of Procedures.

### **7.6 Pulse Oximetry**

Pulse oximetry will be performed as noted in the Schedule of Procedures.

### **7.7 Neurologic Exam**

A neurological exam will be performed as indicated in the Schedule of Procedures.

### **7.8 Concomitant Medications**

All concomitant medication and therapies will be documented at time of apheresis and then from the time of initial CAR T cell infusion through 28 days following final CAR T cell infusion or removal from protocol therapy, whichever occurs earlier. IV contrast is not considered a concomitant medication.

## **7.9 Adverse Events**

Information regarding AEs will be captured following the start of the CAR T cell infusion through 28 days following final CAR T cell infusion per Section 11 Adverse Events and Serious Adverse Events. Related AEs will continue to be followed past Day 28 through resolution, if possible. This study will utilize the NCI CTCAE v5 for toxicity reporting and grading, except for CRS which will be assessed using the CRS Grading Scale in Section 11.5 Cytokine Release Syndrome Grading. Individual neurologic symptoms should be graded using CTCAE v5, however cumulative neurologic toxicity will be graded per Appendix 4 – Neurologic Toxicity Grading System. The study team should have access to the CTCAE v5 which can be downloaded from the Cancer Therapy Evaluation Program (CTEP) website (<http://ctep.cancer.gov>). Refer to Section 11 for information on reporting AEs.

## **7.10 Pregnancy Test**

Female subjects of childbearing potential will have urine or serum pregnancy tests as indicated in the Schedule of Procedures.

Additional pregnancy tests will be performed at any visit in which pregnancy status is in question. A serum pregnancy test will be performed in the event of a positive or equivocal urine pregnancy test result.

## **7.11 Hematology**

Hematology must include complete blood count (CBC) including hemoglobin, hematocrit, red blood cell count, white blood cell count, white blood cell differential, and platelet count and will be obtained according to the Schedule of Procedures.

## **7.12 Chemistry**

Chemistry must include serum sodium, potassium, chloride, bicarbonate, blood urea nitrogen (BUN), creatinine, alanine aminotransferase (ALT), total bilirubin, conjugated bilirubin, and C-reactive protein (CRP) and will be obtained according to the Schedule of Procedures.

## **7.13 Cytokine Release Syndrome Labs and Evaluation**

CRS labs and evaluation will be obtained daily during periods of Grade 2-4 CRS. CRS labs must include CRP, LDH, PT, PTT, ferritin, d-dimer, fibrinogen and absolute lymphocyte count. CRS evaluation must include temperature, heart rate and blood pressure.

## **7.14 Virology**

Virology must include human immunodeficiency virus (HIV) antigen and antibody, Hepatitis B surface antigen, and Hepatitis C antibody testing and will be performed per the Schedule of Procedures. If Hepatitis C antibody testing is positive, quantitative PCR will be performed. Results of virology testing obtained up to 3 months prior to enrollment will be accepted for subject eligibility.

### **7.15 Cerebrospinal Fluid (CSF) Sampling**

Cerebrospinal fluid sampling via intraventricular catheter will be performed according to institution standard practice at the time points indicated in the Schedule of Procedures. All CSF samples may be obtained via CNS catheter. If CSF collection via catheter is not feasible the sample is not required.

Specific testing requirements are noted in the Schedule of Procedures.

Per Section 6.4 Management of Non-CRS Toxicity Associated with Infused CAR T Cells into the CNS, in subjects who develop neurologic toxicity additional cerebrospinal fluid assessments should be considered if clinically indicated.

### **7.16 Correlative Sciences**

Peripheral blood and CSF samples will be collected at the time points specified in the Schedule of Procedures and sent to the CSL. Refer to the study-specific Laboratory Manual for specimen type, storage, and shipping requirements.

Specimens may be processed for molecular analysis of T cell persistence and/or flow cytometric analysis based on detection of EGFRt in conjunction with T cell surface markers. These samples may also be used to detect the *in vitro* anti-B7-H3 activity of the persistent CAR T cells and for serum cytokine analysis. Additionally, DNA-based testing may be done to detect low levels of malignant cells.

If a subject develops systemic toxicity possibly, probably, or definitely (Section 6 Management of Toxicities and Complications) related to CAR T cells, peripheral blood for may be requested to be sent to the CSL up to once per day while the subject is experiencing toxicity. The blood may be used for serum cytokine analysis, and, if indicated by clinical data, detection of an anti-CAR or EGFRt immune response.

If a neurologic toxicity occurs, CSF samples may be requested to be sent the CSL for cytokine analysis and presence of CAR T cells.

Any material in excess of that needed for protocol required CSL samples will be retained for potential additional analysis related to this trial.

Archival tumor tissue, tumor biopsy/resection, or normal tissue biopsy material obtained for clinical purposes may be sent to the CSL to be tested for evaluation of B7-H3 expression, presence of CAR T cells, evaluation of immune modulation, or additional analysis related to this trial.

### **7.17 CNS Imaging**

MRI brain and spine will occur according to the Schedule of Procedures. Per Section 6.4 Management of Non-CRS Toxicity Associated with Infused CAR T Cells into the CNS, additional CNS imaging should be considered in subjects who develop neurologic toxicity, if clinically indicated.

After month 12 following the final CAR T cell infusion MRI will be performed only as clinically indicated. For all MRIs that occur after the End of Therapy/Early Discontinuation Visit, MRI of the spine is required only for subjects with previous spinal disease, positive CSF cytology, or cause for clinical concern.

## **7.18 Disease Response**

Disease Response will be assessed according to the Schedule of Procedures and as further described below.

### **7.18.1 Disease response assessment during active treatment**

Disease Response will be assessed within 1 week following the last CAR T cell infusion on even courses (e.g., 2, 4...) but may be delayed up to 4 weeks due to clinical or scheduling issues. This evaluation must be performed prior to receiving Week 1 CAR T cell infusion on the subsequent odd course (e.g., 3, 5...).

### **7.18.2 Disease response assessment following active treatment**

Disease Response will be assessed per the Schedule of Procedures at end of therapy/early discontinuation (i.e., the required assessment performed after final CAR T cell infusion), then at months 3, 6, 9, and 12 following final CAR T cell infusion as clinically indicated. After month 12 following the final CAR T cell infusion MRI will be performed only as clinically indicated.

Disease Evaluations are no longer required if progressive disease was confirmed in a prior evaluation.

## **7.19 Post-Treatment Long-Term Follow-Up data collection**

Research participants who receive engineered T cells will be required to participate in long-term follow-up (LTFU) per the guidelines set forth by the FDA's Biologic Response Modifiers Advisory Committee that apply to gene transfer studies to capture delayed adverse events related to the use of lentivirally transduced T cells.

### **7.19.1 Post-treatment long-term follow-up data collection**

For the first 5 years following treatment with CAR T cells, patients will be seen at least yearly. The visit will include an interval medical history and physical exam, specifically eliciting for the development of delayed, related AEs of interest, i.e., malignancy, neurologic disorder, rheumatologic or autoimmune disorder, or hematologic disorder. Unexpected medical problems felt to be related to the CAR T cells will be collected. If subjects are not able to be seen at study site, they may be seen by their primary physician for a physical exam and a blood draw courier kit will be provided to obtain research samples. The physician will be provided with adverse event screening guidelines and will be requested to notify the study team of all new malignancies and unexpected illness felt to be related to the CAR T cells.

Following the first 5 years of LTFU, patients who do not have evidence of persisting gene modified T cells will be contacted yearly by phone for an additional 10 years (for a total of 15

years of LTFU). For those patients who have continued persistence of transferred T cells, they will continue to be seen yearly for LTFU for at least a total of 15 years.

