### 11.3.2 Relationship of adverse event to treatment

The investigator will assess the potential relationship of the AE to investigational product using the following descriptions.

- **Not Related:** This category applies to an AE that is clearly not related to the investigational agent/procedure, beyond a reasonable doubt. That is, another cause of the event is most plausible and/or a clinically plausible temporal sequence is inconsistent with the onset of the event and the exposure to study drug and/or a causal relationship is considered biologically implausible.
- **Unlikely Related:** This category applies to an AE that is doubtfully related to the investigational agent/procedure. That is, another cause of the event is highly likely and/or there is not a reasonable temporal sequence from administration of the study drug or one that follows a known or expected response pattern to the suspected study drug. The event could readily have been produced by a number of other factors.
- **Possibly Related:** This category applies to an AE that follows a reasonable temporal sequence from administration of the study drug and that follows a known or expected response pattern to the suspected study drug, but that could readily have been produced by a number of other factors.
- **Probably Related:** This category applies to an AE that is likely related to the investigational agent/procedure. That is, the AE has a temporal relationship to the administration of the investigational agent(s) or research intervention and follows a known or suspected pattern of response.
- **Definitely Related:** This category applies to an AE that is clearly related to the investigational agent/procedure. That is, the AE has a temporal relationship to the administration of the investigational agent(s) or research intervention and follows a known or suspected pattern of response.

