## 11.7 Serious Adverse Event Reporting

SAEs occurring from the beginning of the first infusion of the investigational product up to and including 30 days after the last infusion of the investigational product will be reported to the study Sponsor or its designee within 24 hours of the investigator becoming aware of the event. SAEs occurring after 30 days following the last treatment with the investigational product, which, in the judgement of the investigator or treating physician, are *possibly, probably or*

***definitely*** related to treatment with the investigational product, will be reported to the study Sponsor or its designee within 24 hours of the investigator becoming aware of the event.

Initial SAE reports must be followed by detailed descriptions. These should include copies of hospital case records and other documents when requested. Telephone reports must be confirmed promptly by written report.

Additionally, the Investigator is responsible for submitting follow-up reports for all SAEs until the SAE has resolved or until the subject's condition stabilizes (in case of persistent impairment), or the study participant dies.

A death (including death due to progressive disease) occurring within 30 days after the last T cell infusion must be reported to the Sponsor or its designee within 24 hours of site awareness of the death whether or not it is considered treatment-related. Any death occurring greater than 30 days after the last T cell infusion must be reported to the Sponsor or its designee within 24 hours of site awareness of the death only if it is possibly, probably, or definitely related to treatment with the investigational product.

The investigator also must notify the IRB/Institutional Ethics Committee (IEC) and/or Institutional Biosafety Committee (IBC) of the occurrence of the SAE, in writing, as soon as is practicable and in accordance with local law. A copy of this notification must be provided to the study Sponsor or its designee.

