| Correlative Sciences: PB         | CAR T cell persistence                  |                                                       | X       |         | X                 | X        | X                 | X        | X                 | X        | X                 | X        | X                 |
|                                  | Replication-competent lentivirus (RCL)  | X                                                     | X       |         | X                 |          |                   |          |                   |          |                   |          |                   |
| MRI brain & spine  |                                                     | X                                                     | X       | X       | X                 |          |                   |          |                   |          |                   |          |                   |
| Adverse events       |                                                     | Continuous                                            |         |         |                   |          |                   |          |                   |          |                   |          |                   |

 If performed for clinical indication. May be obtained from local provider or treating oncologist

 Medical events relevant to subject's disease and treatment, inclusive of infectious disease. If relevant, records pertaining to disease response and/or relapse will be collected.

 Testing at all time points must include cell count and cytology. Any additional material obtained for clinical purposes may be sent to CSL for research testing. Disease Evaluations are no longer required if progressive disease was confirmed in a prior evaluation.

 Timepoints only applicable if ongoing T cell persistence in peripheral blood at the end of protocol therapy/discontinuation visit. CAR T cell persistence testing will be discontinued after a negative result.

 MRI of the spine for subjects with previous spinal disease, positive CSF cytology, or cause for clinical concern. Disease Evaluations are no longer required if progressive disease was confirmed in a prior evaluation.

 The following are Delayed Related AEs of interest that must be reported to the Sponsor: development of a new malignancy, or neurologic, rheumatologic, autoimmune, or hematologic disorder

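### The long-term follow-up rules conflict on whether delayed malignancies and other listed disorders are captured regardless of attribution, so a late malignancy judged unrelated can go unreported to the Sponsor

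*Protocol*

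**What the plan says.** Section 7.19 sets up 15 years of follow-up for everyone who receives engineered cells, in order "to capture delayed adverse events related to the use of lentivirally transduced T cells".

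Section 7.19.1 then gives three collection rules in one paragraph:

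- The yearly visit in the first five years is described as "specifically eliciting for the development of delayed, related AEs of interest, i.e., malignancy, neurologic disorder, rheumatologic or autoimmune disorder, or hematologic disorder".
- For anything else, "Unexpected medical problems felt to be related to the CAR T cells will be collected".
- If the subject cannot attend the study site, an outside physician is asked to "notify the study team of all new malignancies and unexpected illness felt to be related to the CAR T cells".

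The schedule of procedures adds a Sponsor-reporting rule. Footnote 6 of Appendix 2 Table 2 (month 3 to year 5) begins "The following are Delayed Related AEs of interest that must be reported to the Sponsor: development of a new malignancy" and goes on to the non-malignant categories. Footnote 4 of Table 3 (years 6 to 15) says the same.

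Section 11.7 governs late serious events. It confines the reporting duty to "SAEs occurring after 30 days following the last treatment with the investigational product, which, in the judgement of the investigator or treating physician, are" at least possibly related to the product. Section 11.2 lists a secondary malignancy among the criteria that make an event serious.

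**The concern.** Whether a rare late event was caused by the vector or the cells is best judged after all such events have been recorded. If a relatedness judgement decides what is recorded or passed on, the case series available for a later causal assessment is incomplete, and nobody can tell by how much. A final statement that no delayed malignancy was reported would then not mean that none occurred.

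Prior treatment makes this practical. Under Section 3.2.1, DIPG and DMG subjects enter after radiotherapy, and the recurrent and refractory subjects after standard first-line treatment. A new malignancy years later will often have another candidate cause.

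The rules also differ by place. A subject seen by an outside physician falls under a request for all new malignancies. A subject seen at the study site falls under a rule worded for related events.

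**Working it through.** The point turns on wording, and the documents give no figure to reproduce. The check sets the rules side by side and follows an event through them.

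**1. The rules**

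| Place | Event | Relatedness wording | Goes to |
|---|---|---|---|
| 7.19.1, study visit | The listed categories, malignancy included | Yes | Study record |
| 7.19.1, other problems | Unexpected problems | Yes | Study record |
| 7.19.1, outside physician | New malignancies | None on the natural reading | Study team |
| 7.19.1, outside physician | Unexpected illness | Yes | Study team |
| Table 2 footnote 6, Table 3 footnote 4 | The listed categories | Yes, in the label | Sponsor |
| 11.7, more than 30 days after last infusion | SAEs, including secondary malignancy (11.2) | Yes: possibly, probably or definitely related | Sponsor |

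**2. A late malignancy.** Seen by an outside physician, it should reach the study team whatever its cause. Seen at the study site, it is elicited as a related event. In both cases the step from study team to Sponsor is governed by Section 11.7 and the footnotes. Under Section 11.7 a malignancy judged *Unlikely Related* or *Not Related* carries no duty to report, and the judgement may be that of a treating physician.

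**3. Could such a judgement be reached?** Section 11.3.2 reserves *Not Related* for events that are clearly unrelated beyond reasonable doubt. It then explains this as meaning, among other things, that "another cause of the event is most plausible". That is a high bar, and an alternative cause alone need not meet it. *Unlikely Related* is the easier route: it applies where another cause is highly likely or the temporal sequence is not reasonable. Both *Unlikely* and *Possibly Related* allow that other factors could readily explain the event. *Possibly* additionally asks for a reasonable temporal sequence and a known or expected pattern of response. A late malignancy after radiotherapy, of a kind not yet seen with this product, could fairly be placed in *Unlikely*. It would then fall outside Section 11.7.

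**4. The non-malignant categories.** The outside-physician sentence does not name neurologic, rheumatologic, autoimmune or hematologic disorders. They appear only under the *related* wording of Section 7.19.1 and the footnotes. No passage clearly requires them to be recorded regardless of attribution.

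**5. Is there another net?** Section 7.9 follows only related adverse events beyond Day 28. The IND safety reporting period in Section 11.8 ends 30 days after the last infusion. Under Section 7.19.2, persistence testing stops after a negative result, and clonality testing is triggered by rising transgene levels, not by a new malignancy. The medical-history footnotes of Tables 2 and 3 could bring an unrelated event into the record, but they create no duty to tell the Sponsor.

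**The case against.** A reader might infer that malignancies are recorded only once someone has already judged them related, and that local opinion removes them before any study assessment. The documents do not support that.

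- The outside-physician route is the one with no filter for malignancy. On its natural reading, the relatedness phrase there qualifies only the unexpected illness.
- Outside physicians see only subjects who cannot attend the site. Yearly visits are planned for five years, with yearly contact after that, and the site investigator is study staff.
- Both footnotes can be read as naming categories that are reportable as such. They cite no attribution step.
- Having another candidate cause does not make an event unreportable. *Possibly Related* expressly allows for one and is enough under Section 11.7.
- Interval histories, scheduled persistence and RCL testing, and a requested autopsy for deaths on study do not depend on event attribution. An event labelled unrelated is not shown to vanish from the record.
- The screening guidelines given to outside physicians, and any separate gene-therapy follow-up protocol (Section 8.2), are not at hand and may settle practice.

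All of this stands against the broad reading. It does not answer the narrower point. That the footnotes can be read two ways is part of the problem, because sites could apply either reading for 15 years. Section 11.7 is not ambiguous: a late secondary malignancy judged below *Possibly Related* need not go to the Sponsor.

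It is also true that Section 7.19 states its aim as capturing related events. That aim is better served by recording first and attributing afterwards.

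The objection that Sponsor reporting of every new neurologic disorder would be heavy in a CNS-tumour population is fair, and it limits the remedy.

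**Conclusion.** The concern holds as an inconsistency with a real gap. The follow-up passages disagree on whether a new malignancy is captured regardless of attribution, and capture varies with where the subject is seen. Section 11.7 as written lets a late malignancy judged *Unlikely* or *Not Related* go unreported to the Sponsor. For the non-malignant categories, recording regardless of attribution is not clearly required anywhere.

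The size cannot be put in numbers. The documents give neither an expected incidence of late malignancy nor the share that would be judged unrelated, and any count of missed events would only restate an assumed rate. The conclusion rests on two readings: that the relatedness phrase in the outside-physician sentence does not extend to malignancies, and that Section 11.7 applies to secondary malignancies because Section 11.2 makes them serious. Neither the dose-escalation rules nor the dose-limiting toxicity data are affected. The consequence is for the completeness of the 15-year safety record, and the wording should be corrected.

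**What to change.** 1. In Section 7.19.1, Table 2 footnote 6 and Table 3 footnote 4, delete *related*, so that each listed category is recorded when it occurs. Record attribution as a separate field that the Sponsor reviews.
2. In Section 11.7, state that any new malignancy after infusion is reported to the Sponsor regardless of attribution.
3. To contain the load, allow neurologic events explained by documented tumour progression to be recorded without expedited reporting.

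The cost is amendment wording, a CRF field and some extra reports, most of them probably neurologic. No new visits or tests are needed.
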